## Abstract

**Background:**

Splinting as part of the overall post-surgical management of patients after release of Dupuytren's contracture has been widely reported, though there is variation in practice and criteria for using it. The evidence on its effectiveness is sparse, of poor quality and contradictory with studies reporting negative and positive effects.

**Methods/Design:**

A multi-centre, pragmatic, randomized, controlled trial is being conducted to evaluate the effect of static night splinting for six months on hand function, range of movement, patient satisfaction and recurrence at 1 year after fasciectomy or dermofasciectomy. Using a centrally administered computer randomization system consented patients will be allocated to one of two groups: i) splint group who will be given a static splint at approximately 10 to 14 days after surgery to be worn for 6 months at night time only as well as hand therapy; ii) non-splint group, who will receive hand therapy only. The primary outcome measure is the patient-reported Disabilities of the Arm, Hand and Shoulder Questionnaire (DASH). Secondary outcomes are total active flexion and extension of fingers, patient satisfaction and recurrence of contracture. Outcome measures will be collected prior to surgery, 3 months, 6 months and 1 year after surgery. Using the DASH as the primary outcome measure, where a difference of 15 points is considered to be a clinically important difference a total of 51 patients will be needed in each group for a power of 90%. An intention-to-treat analysis will be used.

**Discussion:**

This pragmatic randomized controlled trial will provide much needed evidence on the clinical effectiveness of post-operative night splinting in patients who have undergone fasciectomy or dermofasciectomy for Dupuytren's contracture of the hand.

**Trial Registration:**

Current Controlled Trials ISRCTN 57079614

## Background

### Dupuytren's Disease

Dupuytren's Disease (DD) is a progressive fibroproliferative disorder of the palmar fascial complex of the hand. Fascial bands form nodules and cords and eventually contract causing digital finger flexion contractures where they cross joints, especially in the metacarpophalangeal (MCP) and proximal interphalangeal (PIP) joints of the fingers. The little and ring fingers are most frequently affected. These contractures can lead to severe impairments in hand function[1]. Prevalence is highest in people of Northern European stock. The disease presents most commonly in men in their 5th decade of life and an estimated 20% of men over the age of 60 years are affected. In the UK more than 2 million people have DD many of which will require surgical intervention[1].

### Surgical and post-surgical management

Although pharmacological treatment options are being investigated[2], transection of cords (fasciotomy) or excision of diseased fascial bands (fasciectomy) with or without excision of overlying skin remain the only treatments at present [1,3]Surgery is designed to reverse digital contractures and to restore hand function vital for everyday activities of self-care, work and leisure[4]. Following surgery hand therapy provided by specialist occupational therapists or physiotherapists is seen as integral to the management of these patients and is aimed at reducing swelling, optimising wound healing, restoring finger mobility and maximising hand function[4]. In order to maintain the optimum finger extension achieved through surgical release some surgeons advocate the use of static or dynamic splints for daytime and/or night time to be worn up to 6 months. The aim of the splint is to provide prolonged stretch to healing tissues and prevent flexion contractures. Whilst the effectiveness of surgical excision is well established the benefit of different post-operative interventions including static splinting and their effect on functional outcomes remain undecided.

### Evidence on effectiveness of splinting is low quality and inconclusive

Surveys of practice among hand surgeons [5] have highlighted wide variation in the use of post-operative splints [6,7], largely due to a lack of good quality evidence to support their use.

The evidence that does exist regarding post-operative splinting is inconsistent reporting both negative [8](loss of finger flexion, delayed return to function and increased recurrence) and positive (improved scar extendibility, reduced finger extension deficits and delayed recurrence)[9] effects. Research to date is inconclusive due to the available studies being observational, small scale and heterogeneous in terms of the interventions (i.e. type of splint and wearing regimens) and assessment of outcomes.

### The need for a trial

Severe Dupuytren's contracture requiring release accounts for approximately 12,000 patients undergoing surgery in the UK per year [10]. Despite the fact that evidence on the effectiveness of post-operative interventions including splinting remains scarce it remains widely used in practice. A recent survey of 573 orthopaedic consultants in the UK showed that 33% of surgeons used splinting most or all of the time [7]. Another UK survey of 141 surgeons of various grades found that 84% advocated the use of a thermoplastic night splint, however duration of wear differed widely ranging from a few weeks to 6 months[6].

Custom-made splints are costly in terms of material and therapists' time to fabricate. For the patient they may be cumbersome and inconvenient to wear even if only at night-time, which in turn may affect adherence. Also, there is some controversy over the amount of tension [11] and the effect of tension on diseased fascia with some in vitro studies indicating that this can accelerate the fibroproliferative turnover, possibly speeding up recurrence and extension of contractures[12].

On the other hand there is also evidence that they may help in maintaining extension of digits especially where the PIP joint is involved. The rationale for using splints is that they provide continuous low-load tension to healing tissues and thus help to elongate scar tissue[11], which other modalities such as active and passive hand exercises can also achieve but which can be time-consuming for patient and therapists. In the absence of any high quality evidence to support post-operative splints their widespread use may no longer be justifiable to purchasers, providers or patients.

## Methods

### Objectives of the trial

To compare the effectiveness of post-operative static night splinting additionally to standard post-operative hand therapy in improving patient reported hand function, total active movement, patient satisfaction and recurrence at one year.

### Design

The randomized controlled trial is an accepted methodology for minimizing potential biases and ensuring high internal validity. This study is a pragmatic, multi-centre, randomized controlled trial comparing two interventions: post-operative hand therapy including a static night splint versus post-operative hand therapy without splint.

### Setting

The trial will recruit patients from five National Health Services teaching hospitals across three regions in East Anglia in the UK. All five centres have an orthopaedic service and two centres also include a plastic and reconstructive surgery service making up a total of 15 orthopaedic and plastic surgeons with an interest in hand surgery who regularly undertake fasciectomy and/or dermofasciectomy for Dupuytren's contracture (DC). Post-surgical hand rehabilitation services are provided at each centre by hand therapists (occupational therapists and/or physiotherapists with a special interest in hand injuries). Patients admitted for surgery are either operated on as day-cases or admitted overnight, depending on the extent of surgical excision and overall health status.

### Ethics

This multi-centre trial was approved by the Research Ethics Committees and Research Governance Committees for each participating hospital. Informed, written consent will be obtained from all patients prior to enrolment into the trial.

### Recruitment

Patients referred to the orthopaedic and plastic surgery out-patient clinics with a Dupuytren's contracture will be assessed and screened for eligibility by the consultant surgeons. Those meeting inclusion criteria will be told about the trial and given an information leaflet to take away with them. The waiting times between listing for surgery and actual surgery ranges from 12 to 22 weeks, therefore recruitment and consent will be collected later and closer to the date of surgery. Six to eight weeks prior to surgery patients are sent a full participant information sheet and a consent form with a self-addressed envelope by the trial co-ordinator. Those returning a signed consent form are contacted to arrange a pre-surgical baseline assessment.

### Inclusion and exclusion criteria

The target study population are patients with Dupuytren's disease affecting one or more fingers presenting at hand clinic requiring surgical release by fasciectomy or dermofasciectomy and who have consented to surgery. Exclusions are: patients under the age of 18 years, those unable to give informed consent and patients with Dupuytren's contracture affecting the first web space only.

### Randomization

Patients will be randomized into one of two groups. One group will receive post-operative hand therapy only and the other group will receive hand therapy and a static night splint to be worn for 6 months. Randomization will be stratified by recruiting hospital (5 centres) and surgical procedure (dermofasciectomy or fasciectomy) in block lengths of 4.

Patients are randomized after surgery. This will ensure operating surgeons are unaware of group allocation at the time of surgery. A telephone based central computerised randomization service will be used to generate the allocation sequence and the treating hand therapists will obtain the group allocation just before or at the first post-operative hand therapy appointment by ringing a dedicated telephone number available 24 hours. Neither the patients nor the treating hand therapists can be blinded to group allocation.

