#### Splint group

The use of a static night splint is standard practice in all 5 participating centres for the majority of patients, consequently the provision of the night splint in this trial does not constitute a new intervention. Therapists already have training and experience in manufacturing custom-made splints for DC and local protocols and procedures regarding choice of material and design will be followed. Splints will be static with no dynamic components. The principle of 'no tension' ([11,13]will be used. This involves placing the operated digits in maximum achievable extension without placing tension on the surgical wound. Any non-correctable contractures at the time of surgery will be accommodated in the splint.

Where splints are contra-indicated, for example due to post-surgical complications, the application of the splint is delayed. Patients allocated to the splint group will be asked to wear splints at night-time only for 6 months. They are given a simple splint diary in which they record on a weekly basis how many nights out of 7 they actually wore the splint and reasons for not doing so. The splint diary will be collected at the 3 months and 6 months follow-up visit by the research associates.

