### Blinding

Due to the nature of this study, it is not possible to blind the patient or the treating therapist to the intervention received. The primary outcome measure is the patient-rated DASH and therefore blinded assessment is not possible. Secondary outcomes will be assessed by research associates who will not be blinded to the group allocation.

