### Sample size

Using the DASH [14] as the primary outcome measure, where a difference of 15 points is considered to be a clinically important difference [16] and using a between-group standard deviation of 22 points [18] a total of 51 patients would be needed in each group for a power of 90%. Allowing for a 20% loss to follow-up a total of 128 patients need to be randomized. Based on current surgery rates in the five participating centres and assuming a consent rate of 40–50% of those patients invited to take part we anticipate that the target sample size can be recruited within 16 months.

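### A single stated block length of 4 within each hospital-by-procedure stratum lets an unblinded therapist who tracks the stratum know up to one allocation in three before ringing for it

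*Protocol article*

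**What the plan says.** The Randomization section fixes the scheme: "Randomization will be stratified by recruiting hospital (5 centres) and surgical procedure (dermofasciectomy or fasciectomy) in block lengths of 4". It names one length and mentions no variation. The sequence is generated by a central computerised telephone service. As to who rings and when, "the treating hand therapists will obtain the group allocation just before or at the first post-operative hand therapy appointment". Randomization follows surgery, and "Neither the patients nor the treating hand therapists can be blinded to group allocation".

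Three other sections bear on the point:

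- **Splint group:** "The use of a static night splint is standard practice in all 5 participating centres for the majority of patients".
- **Blinding:** the primary outcome is patient-rated and so cannot be assessed blind, and "Secondary outcomes will be assessed by research associates who will not be blinded to the group allocation".
- **Analysis strategies:** the analysis set is all randomized participants. The model adjusts for baseline DASH, hospital and type of surgery.

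**The concern.** A central service hides the list, but not what can be deduced from it. Once either arm has used both its places in a block of 4, the rest of that block is known to anyone who has followed it. Here the length is published, each sequence runs within one hospital and one procedure, and the person who rings delivers the open treatment and works where splinting is usual for most patients.

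The call comes when the operated hand can already be seen. A therapist who foresees the arm could withhold the call, put it off, or change the order of two patients. A patient who is never rung for is not in the analysis set. Patients rung for in a chosen order are in it, but their arm no longer depends on chance alone. The planned covariates do not capture this, because baseline DASH is collected 4 to 8 weeks before surgery and says nothing about the post-operative hand. With no blinded outcome in the trial, unpredictable allocation is one of its few protections against bias.

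**Working it through.** The plan gives no figure for predictability, so there is none to reproduce.

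**Inputs**

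- Block length 4; strata 5 hospitals × 2 procedures = 10 (Randomization).
- Two arms: "Patients will be randomized into one of two groups". The ratio is not stated. 1:1 is inferred from the equal group sizes in the Sample size section ("a total of 51 patients would be needed in each group for a power of 90"), so each block holds 2 + 2.
- 128 patients to be randomized (Sample size), or 128/10 = 12.8 per stratum if strata are equal.
- The share having dermofasciectomy is not given. It is assumed to be 50%, 15% or 5%.

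**Complete blocks.** There are C(4,2) = 6 equally likely sequences. An allocation is known in advance when one arm's two places are already used.

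- AABB and BBAA: the 3rd and 4th are known, 2 each.
- The other four sequences: only the 4th is known, 1 each.
- Mean per block = (2×2 + 4×1)/6 = 8/6 = 1.333. Share = 1.333/4 = 33.3%.
- By position: 0%, 0%, 33.3%, 100%.
- Always guessing the arm that is behind succeeds (0.5 + 0.667 + 0.667 + 1)/4 = 70.8% of the time, against 50% without blocking.

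**Unfinished blocks.** Simulating 128 patients over 10 strata (1,000 runs) gives about 30% known in advance (95% of runs 26% to 34%) and 69% best-guess success. The 30% hardly moves between dermofasciectomy shares of 50%, 15% and 5%.

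**Alternatives.** The observer tracks the whole stratum. For the random mixes, the observer also knows the set of lengths but not the current one. Mixes were simulated with 128 patients, 10 strata of equal expected size and 300 runs.

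| Scheme | Known with certainty | Best guess right |
|---|---|---|
| Fixed 4, complete blocks | 33.3% | 70.8% |
| Fixed 6, complete blocks | 25.0% | 68.3% |
| Fixed 4, 128 patients | about 30% | about 69% |
| Random 4 and 6 | about 6% | about 68% |
| Random 4, 6 and 8 | about 2% | about 66% |

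Varying the length removes most of the certainty. It does little to the guess rate, because any scheme that keeps the arms balanced favours the arm that is behind. A longer fixed block is a poor substitute: fixed blocks of 6 still leave one in four known.

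**Room for reordering.** The Sample size section expects recruitment within 16 months: 128/16/5 = 1.6 patients per hospital per month. With equal centres and even spacing, successive patients in a stratum are about 30.4/1.6 = 19 days apart if nearly all have one procedure, and about 38 days apart if procedures split evenly.

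**The case against.** The strongest reply is that the usual route to selection bias is closed. Surgeons screen, the trial co-ordinator handles consent by post, and research associates take the baseline before surgery. A consented patient with baseline data who is never randomized can be noticed by the trial team. At the spacing above, two patients in the same stratum on the same day would be uncommon unless theatre lists cluster, and waiting for someone else to use up a place usually means weeks. All of this stands and narrows the opportunity. It does not remove it, since the therapist still decides whether and when to ring for an operated patient.

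Four stronger readings are tempting, and the documents do not support them:

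- **That one in three is the actual share foreseen.** Nothing says that one therapist sees every allocation in a stratum. The Setting section speaks of hand therapists in the plural at each centre. The figure is an upper bound for a fully informed observer.
- **That therapists could hold back patients who are losing extension.** The No splint group section records the reference extension at the first therapy visit and judges loss at later ones. No loss as the protocol defines it exists when the call is made. That section also gives an open, recorded route to a splint, which weakens the motive.
- **That foreknowledge distorts consent.** Consent precedes surgery and allocation.
- **That varied blocks make allocation unguessable.** The table shows otherwise. What is gained is the loss of certainty.

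**Conclusion.** The point holds as an avoidable weakness in a choice that the article states, and it is cheap to correct. It is not evidence that any allocation was manipulated. Its size is at most 33.3% of allocations known in advance in complete blocks and about 30% over the planned trial. This rests on a 1:1 ratio, knowledge of the published length, and an observer who follows the whole stratum; the share is lower where therapists do not pool what they see. The effect on the treatment comparison cannot be calculated from the document, because it depends on how often calls would be withheld, delayed or reordered. It is a recommended improvement and gives no ground for doubting the design as a whole.

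**What to change.** For allocations still to be made:

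1. Have the central service draw block lengths at random (for example 4 and 6, or 4, 6 and 8) and do not disclose the lengths to sites.
2. Release the allocation only after the patient is registered and first-visit active extension is entered. The protocol already has this measured, though under the no-splint arm, so it would need to be taken in every patient before the arm is known. The call would then be made at the visit and no longer just before it.
3. Keep a log of every consented, operated patient who is not randomized, with the reason, and report it by hospital. If recruitment is already complete, this is the part that can still be done.

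The cost is one setting in a system already in place, a sentence or two in the protocol, and a change in the order of steps at the first visit. Imbalance within small strata may be slightly larger. The planned adjustment for hospital and type of surgery deals with that. Sample size and the primary model do not change.

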#### No splint group

Patients allocated to the no-splint group will receive hand therapy as described above only. During the early post-operative phase and especially where the surgical scar crosses the metacarpophalangeal (MCP) or interphalangeal (IP) joints patients may experience loss of extension due to the tendency of scar tissue to contract. Such a loss of finger extension may be temporary and also may respond to other treatment modalities such as active exercises, scar massage etc., however where this does not resolve within a week and exceeds an acceptable threshold patients will be given a splint. The criteria for such protocol deviations have been devised and agreed by all participating centre surgeons and therapists. The first hand therapy visit after surgery will be used to record baseline active extension at MCP and proximal interphalangeal (PIP) joints. On subsequent visits this is reassessed and if loss of extension compared to this baseline is greater than 20° at the PIP joint or greater than 30° at the MCP joint patients will be given a splint. Protocol deviations and reasons for these will be recorded.

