### Outcomes

Surgical release of a Dupuytren's contracture is primarily designed to 'open up' the palm and restore finger extensibility and improve hand function. Past studies of splinting have reported outcomes in terms of total active extension and total active flexion as well as self-reported symptoms, function and disability.

The primary outcome measure is self-reported hand function and disability assessed by the Disabilities of Arm Shoulder and Hand Questionnaire (DASH)[14]. The DASH is a 30-item patient-reported questionnaire designed to measure, symptoms and physical function in patients with musculoskeletal disorders of the upper extremity. There is no disease-specific outcome instrument for Dupuytren's contracture and the validation of the DASH has been done on a wide range of patients including Dupuytren's contracture. Longitudinal construct validity has been assessed in patients including those with DC and the responsiveness assessed by effect size is moderate (ES = 0.5). It has good concurrent validity with the subscales of the SF-36 [15] and test-retest reliability has been found to be excellent (ICC = 0.96) [16].

Secondary outcomes are range of movement, patient satisfaction and recurrence. Range of movement for digits I to IV will be assessed using a Rolyan hyperextension finger goniometer and following a standardised protocol. Total active flexion (TAF) and total active extension (TAE) will be recorded by adding individual DIP, PIP and MCP joint scores. Intra-tester reliability of finger goniometry using a standardised protocol has been shown as acceptable [17] with a within-tester error of less than 5 degrees.

Patient satisfaction will be assessed at 6 and 12 months using an 11 point verbal rating scale (VRS) with the question: How satisfied are you with the overall result of the surgery now? A score of 0 means completely dissatisfied and 10 means completely satisfied.

Recurrence of contracture in the previously operated field [10] will be assessed only at 6 months and 12 months post surgery by MCP and PIP joint extension deficit.

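### Therapists may know the allocation when they take the extension reading that later decides which no-splint patients are splinted, which leaves control-arm crossover open to bias

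*Protocol article*

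**What the plan says.** Four statements in the Protocol article bear on this point.

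- **Timing of allocation (Randomization):** "treating hand therapists will obtain the group allocation just before or at the first post-operative hand therapy appointment". The same section adds that "Neither the patients nor the treating hand therapists can be blinded to group allocation".
- **Timing of the reference reading (No splint group):** "The first hand therapy visit after surgery will be used to record baseline active extension at MCP and proximal interphalangeal (PIP) joints".
- **Use of the reference reading (No splint group):** extension is measured again at later visits, and where the loss from the reference is "greater than 20° at the PIP joint or greater than 30° at the MCP joint patients will be given a splint". The section presents this as a protocol deviation for loss that has not settled within a week. The criteria were agreed by surgeons and therapists at all centres, and "Protocol deviations and reasons for these will be recorded".
- **Usual practice (Splint group):** "The use of a static night splint is standard practice in all 5 participating centres for the majority of patients".

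Analysis strategies specifies intention-to-treat with all randomized participants.

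**The concern.** The splinting rule for the no-splint arm works on a difference: the reference extension minus a later extension. An error in the reference carries over degree for degree into that difference. If the therapist already knows that a patient is in the no-splint arm, the reference can be shaded, consciously or not. Recording too much extension makes a later loss look larger and the patient more likely to be splinted. Recording too little does the opposite.

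The reference is the one reading in the rule that could be taken before anyone knows the arm. The protocol does not require this, and its wording expressly permits the opposite order. At stake is how many no-splint patients receive the trial's experimental treatment for reasons other than their true loss of extension. Under intention-to-treat, excess crossover pulls the two arms together, and suppressed crossover leaves them further apart than the agreed rule intends.

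**Working it through.** **Order of events.** The allocation call may come before the appointment or at any time during it. The reference reading comes during it. No section puts the reading before the call, and none gives it to an independent or blinded person. The document does not say outright who takes the reading. That it is the treating therapist is inferred from its being done at the hand therapy visit. So an allocation-aware reference is permitted, and for a call made before the appointment it is the expected order.

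**The plan's own figure first (Sample size).** Inputs: difference 15 DASH points, SD 22, power 90%. Alpha is not stated; two-sided 5% is assumed.

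- n per group = 2 × (22 × (1.960 + 1.282) / 15)² = 45.2, so 46 (47 by t-test). The plan states 51.
- With 51 per group, SE = 22 × √(2/51) = 4.357 and 15/4.357 = 3.443, which gives 93.1% power.
- Loss to follow-up: 102/0.8 = 127.5, so 128, as stated.

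The 51 is larger than these inputs need, so it errs on the safe side. It has no bearing on this point.

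**How sensitive crossover is to the reference.** The document gives no crossover rate and no distribution of loss, so both scenarios below are assumptions. Loss at the worst PIP joint is taken as Normal, and the MCP criterion and the one-week condition are left out. The shift is 5°. That scale is borrowed from the Outcomes section, which describes goniometry "with a within-tester error of less than 5 degrees". The document does not estimate any directional bias.

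Crossover c = P(loss > 20 − s), where s is the over-reading of reference extension:

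| Assumed loss | s = −5° | s = 0 | s = +5° |
|---|---|---|---|
| Mean 10°, SD 10° | P(Z > 1.5) = 6.7% | P(Z > 1.0) = 15.9% | P(Z > 0.5) = 30.9% |
| Mean 5°, SD 8° | P(Z > 2.5) = 0.6% | P(Z > 1.875) = 3.0% | P(Z > 1.25) = 10.6% |

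**From crossover to power.** Assume that a splinted control gains the full splint effect. The diluted difference is 15 × (1 − c), and power = Φ(15 × (1 − c)/4.357 − 1.960); the other tail is negligible.

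| Assumed loss | s = −5° | s = 0 | s = +5° |
|---|---|---|---|
| Mean 10°, SD 10° | 14.0 points, 89.5% | 12.6 points, 82.6% | 10.4 points, 66.3% |
| Mean 5°, SD 8° | 14.9 points, 92.8% | 14.5 points, 91.6% | 13.4 points, 86.8% |

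The effect of shading is the move away from the middle column. The drop from 93.1% to the middle column is crossover that the agreed rule would produce without any bias.

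**The case against.** The strongest reply is that reordering one telephone call protects only one of the two readings. Later extension is also measured in hand therapy by people who know the arm, and a therapist inclined to splint could shade that reading just as easily. This stands: the remedy is partial.

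Next, the plan has safeguards: numeric criteria agreed across centres and a record of each deviation with its reason. They do limit discretion and will show how much crossover occurred. They cannot show whether the reference was shaded, because the thresholds are applied to a difference that contains it.

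It can also be said that the order of tasks within an appointment belongs in a therapist manual that a condensed article need not reproduce. That would hold if the article were silent, but it states the timing, and the stated timing allows the wrong order.

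Several stronger readings are tempting but lack support:

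- **Failed concealment or a directly biased primary outcome.** Allocation comes from a central service after surgery, and the DASH is completed by the patient. Neither is challenged here.
- **A spoiled covariate or recurrence reference.** Baseline range of movement is measured before surgery by research associates, and recurrence is assessed separately at 6 and 12 months. The first-visit reading has no stated use other than the splinting rule.
- **Complications found after an early call.** The Splint group section already provides for delayed application.
- **A fall in power from 93% to about 67% because of this flaw.** That is the effect of 30% crossover compared with none. In the first scenario above, about half of that crossover would arise under the rule with accurate readings.

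**Conclusion.** The point holds as a weakness in sequence. The stated timing lets the reference reading be taken with the arm known, nothing else in the document prevents it, and this opens a route to biased control-arm crossover and a distorted intention-to-treat contrast.

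The size cannot be fixed from the document, and nor can the direction. Under the assumptions shown (Normal loss, a systematic 5° shift in every control, full benefit in splinted controls, 51 analysed per arm, SD 22, two-sided 5%), over-reading lowers power from about 83% to 66% or from about 92% to 87%. Under-reading raises it to about 89% or 93%, by withholding splints that the rule would have given. These figures are probably on the high side, since a borrowed measurement error is treated as a uniform bias and the one-week condition is ignored.

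A reader might infer that therapists will shade the reading, or that the trial will lose this much power. The document supports only that the opportunity exists. The change is still worth making, because it closes one route to bias at very little cost.

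**What to change.** In the Randomization section, delete 'just before' and state that the therapist telephones for the allocation only once the patient has attended the first hand therapy appointment and the baseline active MCP and PIP extension has been written down, for example on the treatment checklist already in use. Put the same order in the therapist instructions. Leave the splinting thresholds as they are; no view is taken on them.

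The cost is small. Both tasks already belong to one visit, and the telephone line is open 24 hours. No visit, treatment or sample size changes. The one drawback is less notice for scheduling the making of a custom splint, which the Background describes as costly in therapists' time. The change does not blind the later readings, so part of the weakness remains and should be acknowledged when crossover is reported.
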